| Myalgia                  | 0                                     | 0                                     | 5/14                          | 3/10                                |
| Arthralgia               | 0                                     | 0                                     | 4/14                          | 1/10                                |
| Skin rash                | 0                                     | 0                                     | 1/14                          | 1/10                                |

The results of these trials are detailed in the Investigator's Brochure. In summary, no serious adverse events (SAEs) or thrombotic complications were reported, and very few possible adverse drug reactions (ADRs) were observed. The most common adverse events reported were myalgia, arthralgia, and skin rash. These were generally mild and resolved during or shortly after cessation of dosing. Direct evidence was obtained that these monoclonal antibodies contributed to the temporary containment of HIV-1 replication in infected humans.

Further analyses and experiments in relation to these clinical trials were recently reported, which investigated the possibility of autoreactivity and possible thromboembolic disorders associated with C4E10 and C2F5. During trial 4 (as above table) the study design was modified to collect prospective data from the last four high-dose patients. Very mild (<1.25 x ULN) prolongation of the APTT 30 minutes post-infusion was observed which rapidly remitted, and there was no effect on the PT. In vitro experiments indicated that the effect on coagulation profile was mediated by 4E10. Further analyses indicated that C4E10, but not C2F5, also showed low-level cross-reactivity with cardiolipin, and that infusion of C4E10 resulted in transient low anti-cardiolipin antibody titres. It was concluded that there was little evidence that the monoclonal antibodies conferred an increased risk of thrombosis, but that monitoring of both coagulation parameters and anti-phospholipid antibodies should be carried out in any further clinical trials.

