#### 5.5.2 Secondary endpoints:

- 24 hours post-1st dose, and 36 hours post-12th dose cervico-vaginal lavage MAb levels
- 24 hours post-1st dose, and 36 hours post-12th dose Mab levels in self-sampled vaginal aspirate
- 8 hours post-1st dose, and 12 hours post-12th dose serum MAb levels
- Number of grade 3 or above genital adverse events (see Appendix 6) during the dosing or follow up period
- Number of grade 3 or above other clinical or laboratory adverse (see Appendix 7) events confirmed at examination or on repeat testing respectively during the dosing or follow up period
- Number of events attributable to the study gel leading to discontinuation of gel

Data on local events listed above will be solicited with specific questions and/or cervico-vaginal and colposcopic examination. Data on laboratory events will be collected through the routine tests or in response to a clinical event. Data on other events will be collected with open questions. Detail on the analysis of MAbs in vaginal secretions and serum samples can be found in section 10.4.

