### **7.6 Telephone calls**

A Clinical Investigator will telephone the participant on two occasions during the dosing period (day of the 2nd to 4th and 8th to 10th doses). The Investigator will check on the participant's condition, record information about any adverse events experienced or medication used and check they are using the gel on a daily basis. The Investigator will enter the data collected into the participant's file.

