## **9.5 Temporarily halting or stopping the study**

In the case of 3 women experiencing either a grade 3 or above genital adverse event or grade 3 or above clinical or laboratory adverse event, the study will be temporarily halted pending unblinded review by the Data Monitoring Committee (DMC). Several severe or

serious AEs, which are probable in relation to the study gel, will lead to the study being terminated at that point. The decision to stop the study rests on the CI, with recommendations from the DMC (see section 11.6.3).

The Sponsor reserves the right to terminate the study at any time.

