### Abbreviations:

|                |                            |     |                       |
|----------------|----------------------------|-----|-----------------------|
| ULN            | Upper Limit of Normal      | LLN | Lower Limit of Normal |
| R x | Therapy                    | Req | Required              |
| Mod            | Moderate                   | IV  | Intravenous           |
| ADL            | Activities of Daily Living | Dec | Decreased             |
| OTC            | Over the counter           |     |                       |

The tables below define clinically significant abnormal pathology results which are classed as AEs. Any results that are outside of the normal range for the laboratory at York Hospital but do not meet the criteria for being classed as an AE will not be classed as such. For events or results that are not specified in the tables, a decision will be made by the CI or a trial physician, as delegated by the CI, as to whether the result is clinically significant. Only those events or results that are deemed clinically significant will be classed as AEs.

For clinical events not specified in the tables below the following grading should be applied:

- *Grade 1 (mild)*: Awareness of sign or symptom but tolerated with minimal or no interference with ADLs. Transient (< 48 hours). May be relieved by OTC medication but no other medical intervention required.
- *Grade 2 (moderate)*: Notable symptoms resulting in greater than minimal interference with ADLs. No or minimal medical intervention required.
- *Grade 3 (severe)*: symptoms causing significant incapacity resulting in bed rest or activity reduced by >50% of usual level and/or unable to work. Medical intervention required.
- *Grade 4 (extreme/life-threatening)*: Significant medical intervention/therapy required; hospitalization required to prevent permanent impairment or death.

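### Non-genital grade 3+ clinical events enter the safety endpoint only if confirmed by examination, so a severe event that resolves first is missing from it although it stops gel and counts toward halting the study

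*Protocol*

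**What the plan says.** **Endpoint.** Section 5.5.2 makes the number of grade 3 or above other clinical or laboratory adverse events a secondary endpoint, limited to "events confirmed at examination or on repeat testing respectively during the dosing or follow up period". Section 10.2.2 carries the same restriction into the planned comparison of the three groups. The genital endpoint has no such condition: "Number of grade 3 or above genital adverse events (see Appendix 6) during the dosing or follow up period".

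**Collection.** For events that are neither local nor laboratory, section 5.5.2 says "Data on other events will be collected with open questions". Under section 7.6 an investigator telephones twice during dosing, on the day of doses 2 to 4 and of doses 8 to 10, to "record information about any adverse events experienced or medication used". Table 7-1 marks a general physical examination at visits 1 and 8 only. Clinic visits in the dosing cycle have cervico-vaginal examination and colposcopy.

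**Grading.** For clinical events not listed in Appendix 7, grade 3 means "symptoms causing significant incapacity resulting in bed rest or activity reduced by >50% of usual level and/or unable to work", with medical intervention also required.

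**Actions.** Section 9.4.2 discontinues gel for a clinical or laboratory event of grade 3 or above. Section 9.5 applies once three women have had a genital event of that grade or a "grade 3 or above clinical or laboratory adverse event, the study will be temporarily halted" pending unblinded review by the Data Monitoring Committee. Neither section asks for confirmation.

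**The concern.** The endpoint sets a condition that the collection method will not always be able to meet. A woman may report by telephone, or at her next visit, a severe episode that is already over. A clinician can grade it from her account, and the discontinuation and halting rules then apply to it. Nothing remains to be confirmed by examination, so read as written the endpoint scores zero for that event.

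Two things are at stake. First, the only count of severe non-genital clinical events can understate what happened, in a trial with about 10 women per arm (30 randomised 1:1:1), where each such event matters. Second, the safety table may not reconcile with the trial's own record: women could have stopped gel, or the study could have been halted, for events that the grade 3+ table does not show.

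**Working it through.** The protocol gives no event rate, effect size or power for the safety endpoints (10.1 says there was no information for power calculations), so there is no figure to reproduce. The check compares sections and then adds one illustration with stated assumptions.

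**Step 1: which condition applies to which event.** The word respectively in the endpoint pairs clinical events with examination and laboratory events with repeat testing. A repeat test cannot stand in for an examination of a clinical event.

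**Step 2: whether an examination is built in.** Collection is by open question and telephone. Between screening and visit 8 the scheduled examinations are genital. The protocol does not define confirmation, set a time limit for it, or require an unscheduled examination after a severe report.

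**Step 3: whether grade 3 can be reached without findings that persist.** In some cases it can. Appendix 7 includes headache that is intractable or needs repeated prescription medication, more than 10 loose stools a day, and myalgia severe enough that she cannot climb stairs. The default rule for unlisted events turns on bed rest, reduced activity or inability to work.

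**Step 4: trace one event.** Take a severe headache reported at the second telephone call, given prescription medication, and gone before visit 6.

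| Place in the protocol | Treatment of this event |
|---|---|
| 9.4.2 Discontinuation | Triggers it; no confirmation needed |
| 9.5 Halting | Counts as one of the three women; no confirmation needed |
| 5.5.2 and 10.2.2, grade 3+ other clinical events | Not counted unless someone examined her in time |
| 5.5.2, events leading to discontinuation | Counted only if attributed to the gel; 10.2.2 merges this with the genital count |
| 10.2.2, all adverse events | Counted, with all grades together |
| 10.2.2, possibly or probably related events | Counted only if so classed, with all grades together |

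No row other than the third gives a grade 3+ count for this class. An event after dose 12 cannot lead to discontinuation, so it appears only in the comparisons that ignore grade.

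**Step 5: what this could do to reconciliation (illustration).** Suppose three women halt the study, each with one other clinical event, and each event is confirmed independently with probability c. The protocol does not give c; 75%, 50% and 25% are assumed.

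- P(fewer than 3 counted) = 1 − c³
- P(none counted) = (1 − c)³

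| Assumed c | Fewer than 3 counted | None counted |
|---|---|---|
| 75% | 1 − 0.422 = 0.578 | 0.25³ = 0.016 |
| 50% | 1 − 0.125 = 0.875 | 0.5³ = 0.125 |
| 25% | 1 − 0.016 = 0.984 | 0.75³ = 0.422 |

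With no confirmation condition (c = 1), all three are always counted.

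**The case against.** A sensitive stopping trigger beside a more specific endpoint is a coherent design. The two serve different purposes and need not count identical events. Participants are protected either way, because 9.4.2 and 9.5 act on unconfirmed events. The events also stay in the analysis: 9.3.2 requires all adverse events to be analysed, and 10.2.2 compares them without confirmation. Participants may contact the team at any time (7.2.4), and a grade 3 report leads to discontinuation, so a prompt unscheduled examination is plausible. All of this stands, and it limits the point to one secondary endpoint. It does not restore a complete grade 3+ count.

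A reader might infer four stronger claims, none of which the protocol supports.

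- **That the rule hides the known coagulation effect.** Section 3.4 reports that "prolongation of the APTT 30 minutes post-infusion was observed which rapidly remitted", but it was below 1.25 × ULN, and section 13.4 puts it at grade 1 or below. Grade 3 APTT in Appendix 7 starts above 2.33 × ULN, so that pattern does not reach this endpoint with or without a repeat test. Repeat testing of laboratory results is a defensible guard against artefact.
- **That most grade 3 clinical definitions rest on history.** Many in Appendix 7 rest on signs, measurements or treatment given, such as arrhythmia, bronchospasm, rash and fever. The default definition also requires medical intervention, which implies some medical contact.
- **That the transient events the protocol expects would be lost.** Section 3.4 describes the earlier myalgia, arthralgia and rash as generally mild. The local effects foreseen in 13.4 are usually mild and genital, and genital events need no confirmation.
- **That half to four-fifths of short severe events would go uncounted.** This comes from matching assumed 2- or 3-day events to scheduled visits with no unscheduled examination. For onset on study days 3 to 12, with visit 5 on day 5, 6 or 7 and visit 6 on day 13, a 2-day event overlaps a visit for 3 of 10 onset days and a 3-day event for 5 of 10. A 5-day event overlaps for 7 to 9 of 10. The answer depends on the assumed duration.

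**Conclusion.** The concern holds for non-genital clinical events. As written, the endpoint leaves out a grade 3+ event that resolves before examination, while 9.4.2 and 9.5 act on that same event, and no other planned comparison supplies the missing grade 3+ count. The wording is fixed in the protocol's own endpoint definition and repeated in its analysis section, so it is not a detail left to a statistical analysis plan.

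The size of the loss cannot be derived from the document. It depends on how many such events occur, how long they last and how often an unscheduled examination takes place, none of which is stated. The probabilities above show only how the endpoint and the halting record could diverge under assumed confirmation shares, one event per woman and independence. The documents give no reason to expect the loss to differ by arm under blinding, so this is a possible undercount and a reconciliation problem, not a demonstrated bias between groups. It is a cheap improvement to a secondary endpoint and does not threaten the primary pharmacokinetic analysis.

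**What to change.** In 5.5.2 and 10.2.2:

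- **Clinical events.** Count every grade 3 or above other clinical event as graded by a study clinician under Appendix 7, whether it came to light by history, telephone or examination. Report those confirmed by examination as a subset.
- **Laboratory events.** Keep confirmation on repeat testing, and show the count of all grade 3 or above results beside the confirmed count.

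The safety table can then be reconciled line by line with the discontinuation and halting record. No change to the discontinuation or halting rules is proposed.

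The cost is a wording change in two sections, since the events are already recorded. The drawback is that some unverified symptom reports enter the main count. In a blinded, placebo-controlled trial that is a small price, and the confirmed subset lets a reader see how much depends on them.

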## **5.6 Duration**

All study procedures will be carried out over three to four consecutive menstrual cycles. The screening visit will take place between two and six weeks before the first dosing visit. Dosing with the randomised study gel will begin between days 7 and 13 of the second or third menstrual cycle, and participants will administer the study gel once daily for twelve days. Further genital examinations with systemic and genital tract samples will be taken 12 & 36 hours after the last dose. The final follow up visit will take place between days 7 and 21 of the subsequent menstrual cycle.

## **5.7 Sub-studies**

We will conduct three sub-studies relating to the exploratory objectives of the study: 1) investigation of the impact of Mabgel on vaginal flora; 2) comparison of self-sampled, to clinician-sampled vaginal secretions and 3) Investigation of the experience of taking part in the clinical trial. Further details are provided in section 12.2.

## **5.8 Organisational summary**

**Co-Sponsors:** York Hospitals NHS Foundation Trust and the University of York

**Funder:** European Commission (European Microbicide Programme)

**Co-ordinator:** [name] [name]

## **6. RECRUITMENT OF PARTICIPANTS**

### **6.1 Inclusion criteria**

- Females
- Aged  $\geq 18$  and  $\leq 45$  years
- In good health as determined by medical history, physical examination and clinical judgement
- Willing and able to give written informed consent
- Available for the duration of the study
- Willing to undergo screening for HIV, Hepatitis B & C, and sexually transmitted infections
- Willing to abstain from vaginal practices including receptive oral sex and sexual intercourse from 48 hours before the first dose of the study gel until after visit 7
- If physiologically fertile, using a reliable method of contraception for the 3 to 4 menstrual cycles covering the pre-study, study dosing and follow up cycle to visit 8 (methods defined as one of: consistent use of condoms with every act of sexual intercourse; combined oral contraceptive pill; desogestrel-containing progesterone only pill (Cerazette); intra-uterine contraceptive device or system; injectable contraceptive; progesterone implant)
- Willing to abstain from using any genital preparations, other than the study gel, during the period of gel administration until after visit 7
- Willing to abstain from using tampons during the period of gel administration until after visit 7
- Judged by clinician to be able, and likely, to comply with the procedures required as set out in the protocol
- Have been registered with a GP for at least the past 3 months
- Response received from GP before randomisation
- Have access to a domestic refrigerator at home for the purposes of storing the study gel

### **6.2 Exclusion criteria**

- Untreated syphilis, gonorrhoea, trichomonas, chlamydia, vaginal candidosis or bacterial vaginosis
- Clinically significant (out of the normal range and deemed clinically significant by the CI or study physician) haematological, biochemical, immunological or coagulation assay abnormalities on screening
- HIV infection, anti-HCV antibody positive, HbsAg positive
- Abnormal findings on pelvic examination, deemed clinically significant by the CI or study physician
- History of coagulation or thrombotic disorders
- Significant current general medical illness
- Irregular menstrual bleeding likely to cause vaginal bleeding during the dosing period as judged by the CI or study physician
- Current participation, or participation within the last 2 months in another clinical trial
- Treatment for cervical intraepithelial neoplasia (CIN) or other gynaecological instrumentation of the cervix within the past 3 months
- Pregnant, within 12 weeks postpartum, or breast feeding
- Unlikely to comply with protocol
- Have any condition which, in the opinion of the CI or study physician, might interfere with the evaluation of the study objectives

- Unable to fluently read and speak English to a level adequate for the full comprehension of procedures required in participation and consent

### **6.3 Number and source of participants**

We will aim to recruit and randomise 30 healthy HIV negative female volunteers. All 30 participants will be randomised to one of the three trial arms, subject to complete fulfilment of the eligibility criteria.

Participants will be recruited by advertising in the York area, including via the GU medicine clinic, the University of York, York St John University, mailing lists, and by coverage and advertising in local media.

### **6.4 Screening procedures and pre-randomisation investigations**

#### **6.4.1 Informed Consent**

The Investigator has both ethical and legal responsibility to ensure that each participant being considered for inclusion in this study is given a full explanation of the protocol. This shall be documented on a written informed consent form (Appendix 3) that shall be approved by the same Research Ethics Committee (REC) responsible for approval of this protocol. Each informed consent form shall include the elements required by UK Clinical Trials Regulations and FDA regulations in 21 CFR Part 50 and must adhere to the ethical principles that have their origin in the Declaration of Helsinki.

Participants will be provided with a detailed written participant information leaflet no less than 24 hours before attending for the screening visit. A brief version of the participant information leaflet is also available to be used as an optional aid when explaining key information regarding the trial. Participants will also be given a full verbal explanation of the trial before providing informed consent. Once the appropriate essential information has been provided to the participant and fully explained by a Clinical Investigator, and it is felt that the participant understands the implications of participating, the REC-approved written informed consent form shall be signed and dated by both the participant and the Investigator obtaining consent, who must be a physician. The participant will be given a copy of the signed informed consent form; the original will be kept in the trial master file by the Investigator and a copy will be kept in the participant's file. All of the above mentioned activities must be completed before the participant can take part in the trial.

At the point when a potential participant contacts the research team to indicate their initial interest in the study (this will usually be by telephone in response to an advertisement) the Investigator may discuss the availability of the study and the possibility for entry with a potential participant without first obtaining consent. The following general eligibility questions may be discussed prior to conducting informed consent:

- Age
- Sexual activity
- Any current method of contraception
- Availability for the duration of the study
- Menstrual cycle
- General health state

Informed consent must be obtained and documented prior to initiation of any trial-related procedures that are performed solely for the purpose of determining eligibility for research. Answers to the above eligibility questions will be documented as part of the screening visit.

If a procedure is done in anticipation of, or in preparation for, the research, it is considered to be part of the research.

#### **6.4.2 Screening Visit**

Each participant will be assigned a Screening Identification Number (SID). SID numbers will not be reassigned. A master log of screened participants with SID, demographic and locator information must be maintained and kept in the trial master file (kept at the study site in a secure location) to track participants who have been screened for the study. If the participant does not enroll in the dosing part of the trial, study staff will document the reason for not enrolling in the participant register.

At the screening visit, a Clinical Investigator will conduct a general discussion of the trial and the participant's interest in trial participation will be assessed. If the Clinical Investigator determines the participant is eligible (based on the general discussion of the trial and the eligibility criteria and subject to screening) informed consent will be obtained from the female participant by a study physician. Informed consent will be taken prior to the initiation of any trial-related procedures using the informed consent form (Appendix 3). Checks will be made by the study team to prevent over-volunteering.

Once written informed consent is obtained, the following procedures will be conducted according to the Study Schedule (section 7.1):

- Medical, gynaecological, and sexual history
- Details of concomitant medications and allergy history
- Physical examination
- Urine pregnancy test and urinalysis
- HIV, Syphilis, haematology, chemical pathology
- Cervico-vaginal examination, modified colposcopy, and genital infection screen

A record of the above procedures and any findings will be entered into the participant's file.

Following the screening visit, the blood and cervical GC and CT samples will be sent to the pathology laboratory at York Hospital for analysis (the urinalysis, pregnancy test and microscopy for BV, TV and Candida will be carried out at the trial site). During cycle 1 a Clinical Investigator will review the results from the laboratory to determine if participants are eligible for enrolment into the study. Once the laboratory results are obtained, they will be signed and dated by the Investigator within 72 hours of receipt, and the original signed report will be kept in the participant's file.

